### Outcomes

The outcomes will relate to process, resources, management, and scientific feasibility, as outlined below.

#### Process Outcomes

Process outcomes will include assessing recruitment rates (ie, response of participants to recruitment strategies, number of potential participants who remain interested in the study after information and screening, and reasons for refusal to participate).

#### Resource Outcomes

Resource outcomes will include assessing the rates of participant compliance (ie, number of practice activities, teleconference sessions, and one-on-one phone calls completed), attrition (ie, percentage of participants who drop out of the study and reasons for dropping out), suitability of eligibility criteria (ie, percentage of interested participants who meet the inclusion criteria and reasons for exclusion), and total cost of intervention delivery (ie, cost of equipment, personnel, and participant remuneration).

#### Management Outcomes

Management outcomes will include assessing staff time (ie, staff preparation and training time, call time, attempted call time, and report-taking time), use of technical support (ie, number of equipment-related data collection problems and number of technical support calls made by staff and/or participants), intervention fidelity (ie, interventionist’s compliance to the protocol), and efficiency and accuracy of data collection and entry (ie, data completeness and time to collect, enter, and check data).

#### Scientific Outcomes

These will include assessing safety, treatment effect, participant satisfaction with intervention components (ie, intervention content, interventionist, and delivery method), and subjective experience of participating in the intervention.

#### Safety

Safety will involve reporting of adverse events (AEs). AEs are defined as any unfavorable change in health experienced by a participant during the trial period [50]. Each AE will be rated based on severity (grade 1 [mild] through 5 [death]), expectedness, and potential relation to study participation (ie, not related, possibly related, or definitely related) using the National Institutes of Health terminology and classification scheme [50]. AEs will be reported as the overall rate, severity, and characteristics of the AEs.

**Table 1 table1:** Timing, content, and main behavior change techniques in Physical Activity Together for People With Multiple Sclerosis.

Timing, description, and overview of session content					Code for behavior change techniques included in each session		Main behavior change techniques included in each session
**Week 1**							
	**Teleconference 1**						
		**Getting started**		2.3		Self-monitoring of behavior	
			Ground rules for the teleconference sessions	3.3		Social support (emotional)	
			Understanding the basics of physical activity	4.1		Instruction on how to perform the behavior	
			How much physical activity do you need?	5.1		Information about health consequences	
			Is it safe for you to participate in physical activity?	5.4		Monitoring of emotional consequences	
			Setting up a physical activity program	9.1		Credible source	
			Recording your baseline physical activity	N/A^a^		N/A	
			Explanation of practice activity	N/A		N/A	
**Week 2**							
	**Phone call 1**						
		Monitoring and providing individualized support, advice, and encouragement		1.2		Problem solving	
		Promoting accountability, maintaining motivation, and troubleshooting		3.2		Social support (practical)	
		N/A		9.1		Credible source	
**Week 3**							
	**Teleconference 2**						
		**Dyadic coping**		1.1		Goal setting (behavior)	
			Review material from last session	1.2		Problem solving	
			Understanding dyadic coping	3.3		Social support (emotional)	
			Setting physical activity goals	4.1		Instruction on how to perform the behavior	
			Setting goals in PAT-MS^b^ physical activity log	8.1		Behavioral practice	
			Explanation of practice activity	9.1		Credible source	
**Week 4**							
	**Phone** **call 2**						
		Monitoring and providing individualized support, advice, and encouragement		1.2		Problem solving	
		Promoting accountability, maintaining motivation, and troubleshooting		3.2		Social support (practical)	
		N/A		9.1		Credible source	
		N/A		10.4		Social reward	
**Week 5**							
	**Teleconference 3**						
		Action planning		1.2		Problem solving	
		Review material from last session		1.4		Action planning	
		What can physical activity do for people with multiple sclerosis?		1.5		Review behavior goals	
		What can physical activity do for support partners?		1.6		Discrepancy between current behavior and goal	
		Developing an action plan for meeting physical activity goals		2.3		Self-monitoring of behavior	
		Explanation of practice activity		5.1		Information about health consequences	
		N/A		8.1		Behavioral practice	
		N/A		8.7		Graded tasks	
		N/A		9.1		Credible source	
		N/A		10.4		Social reward	
**Week 6**							
	**Phone call 3**						
		Monitoring and providing individualized support, advice, and encouragement		1.2		Problem solving	
		Promoting accountability, maintaining motivation, and troubleshooting		3.2		Social support (practical)	
		N/A		9.1		Credible source	
		N/A		10.4		Social reward	
**Week 7**							
	**Teleconference 4**						
		**Staying motivated**		1.2		Problem solving	
			Review material from last session	1.5		Review behavior goals	
			Understanding motivation	1.6		Discrepancy between current behavior and goal	
			Staying motivated to increase your physical activity	2.3		Self-monitoring of behavior	
			Explanation of practice activity	7.1		Prompts or cues	
		N/A		8.1		Behavioral practice	
		N/A		8.7		Graded tasks	
		N/A		9.1		Credible source	
		N/A		10.4		Social reward	
**Week 8**							
	**Phone call 4**						
		Monitoring and providing individualized support, advice, and encouragement		1.2		Problem solving	
		Promoting accountability and troubleshooting		3.2		Social support (practical)	
		N/A		9.1		Credible source	
		N/A		10.4		Social reward	
**Week 9**							
	**Teleconference 5**						
		**Building support**		1.1		Goal setting (behavior)	
			Review material from last session	1.2		Problem solving	
			Building a strong support system	1.5		Review behavior goals	
			Types of social support	1.6		Discrepancy between current behavior and goal	
			Explanation of practice activity	2.3		Self-monitoring of behavior	
		N/A		8.1		Behavioral practice	
		N/A		8.7		Graded tasks	
		N/A		9.1		Credible source	
		N/A		10.4		Social reward	
**Week 10**							
	**Phone call 5**						
		Monitoring and providing individualized support, advice, and encouragement		1.2		Problem solving	
		Promoting accountability and troubleshooting		3.2		Social support (practical)	
		N/A		9.1		Credible source	
		N/A				Social reward	
**Week 11**							
	**Teleconference 6**						
		**Final tips**		1.1		Goal setting (behavior)	
			Review material from last session	1.2		Problem solving	
			Making physical activity a life-long habit	1.5		Review behavior goals	
			Closing comments	9.1		Credible source	
		N/A		9.3		Comparative imagining of future outcomes	
		N/A		10.4		Social reward	
**Week 12**							
	**Phone call 6**						
		Monitoring and providing individualized support, advice, and encouragement		1.2		Problem solving	
		Promoting accountability and troubleshooting		3.2		Social support (practical)	
		N/A		9.1		Credible source	
		N/A		10.4		Social reward	

^a^N/A: not applicable.

^b^PAT-MS: Physical Activity Together for People With Multiple Sclerosis.

#### Treatment Effect

This will involve assessing changes in the following outcomes between T1 (baseline) and T2 (12 weeks): accelerometer-measured PA, self-reported PA, resilience, social support, dyadic relationship quality, quality of life, MS self-efficacy, experiential aspects of participation, and coping. Table 2 provides a summary of the treatment outcomes and psychometric properties of the outcome measures included in the study.

**Table 2 table2:** Treatment effect outcomes, outcome measures, and psychometric properties.

Outcome, outcome measure and psychometric properties				Reliability and validity statistics		Intraclass correlation coefficient
**Change in accelerometer-measured PA^a^ (ie, minutes of sedentary, light, and moderate-to-vigorous activity)**						
	**ActiGraph model GT3X-BT accelerometer [51]**					
		Validity	r_s_=0.61, 95% CI 0.47-0.71		N/A^b^	
		Test-retest reliability	r_s_=0.49, 95% CI 0.40-0.57		0.84, 95% CI 0.81-0.87	
**Change in self-reported PA (ie, total PA minutes)**						
	**Godin Leisure-Time Exercise Questionnaire [52-54]**					
		Convergent validity	*r*=0.38-0.7; *P*<.01		N/A	
		Divergent validity	*r*=−0.32 to −0.45; *P*<.01		N/A	
		Test-retest reliability	*k* coefficient=0.40, 95% CI 0.21-0.60		0.74, 95% CI 0.69-0.78	
**Change in resilience**						
	**Connor-Davison Resilience Scale [55,56]**					
		Internal consistency	Cronbach α=.89		N/A	
		Test-retest reliability	N/A		0.87	
		Convergent validity	*r=*0.83; *P*<.001		N/A	
**Change in social support**						
	**Interpersonal Support Evaluation List-12 [57,58]**					
		Internal consistency	Cronbach α=.82		N/A	
		Convergent validity	*r=*0.33-0.40; *P*<.001		N/A	
**Change in dyadic relationship quality**						
	**Short-form Dyadic Adjustment Scale [59,60]**					
		Internal consistency	Cronbach α=.78		N/A	
		Construct validity	*r*=0.38-0.72; *P*<.01		N/A	
**Change in quality of life among people with MS^c^**						
	**Multiple Sclerosis Impact Scale-29 [61,62]**					
		Reliability	Cronbach α≥.89 for all subscales		N/A	
		Convergent validity	r_s_≥0.57; *P*<.001		N/A	
**Change in quality of life among MS care partners**						
	**Caregiver Quality of Life in Multiple Sclerosis Scale [63]**					
		Internal consistency	Cronbach α≥.75 for all subscales		N/A	
		Test-retest reliability	Weighted *k*≥0.46		N/A	
		Construct validity	N/A		0.96; *P*<.001	
**Change in MS self-efficacy**						
	**Multiple Sclerosis Self-Efficacy Scale [64]**					
		Internal consistency	Cronbach α=.81		N/A	
		Test-retest reliability	*r*=0.81; *P*<.001		N/A	
		Construct validity	r_s_≥0.55; *P*<.01		N/A	
**Change in experiential aspects of participation**						
	**Measure of Experiential Aspects of Participation [65]**					
		Internal consistency	Cronbach α≥.95 for all subscales		N/A	
		Convergent validity	N/A		≥0.62; *P*<.001 for all subscales	
**Change in coping among MS care partners**						
	**Coping with Multiple Sclerosis Caregiving Inventory [66]**					
		Internal consistency	Cronbach α≥.57 for all subscales		N/A	

^a^PA: physical activity.

^b^N/A: not applicable.

^c^MS: multiple sclerosis.

#### Satisfaction With Intervention Components—Content, Interventionist, and Delivery Method

This will be assessed in both people with MS and care partners using a satisfaction survey developed for this study. Items will be scored using a 5-point Likert-type scale, with higher scores reflecting greater satisfaction.

#### Subjective Experience of Participation in All Aspects of PAT-MS

This will be explored in both people with MS and care partners using a semistructured exit interview. Suggestions for intervention improvement and participants’ willingness and concerns regarding future participation in PA will also be explored.

### Data Management and Analysis

#### Quantitative Data Analysis

Data management and analysis will be performed using IBM SPSS Statistics for Windows (IBM Corp). Descriptive statistics, including means and SDs (continuous variables) and frequencies and proportions (categorical variables), will be used to summarize all demographic and feasibility data. Within-subject changes and effect sizes for improvement in scientific outcomes from T1 to T2 will be calculated using Cohen *d* separately for people with MS and care partners and by condition (immediate vs delayed control).

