## Methods

### Study Design

This protocol has been written following both the Standard Protocol Items: Recommendations for Interventional Trials and Consolidated Standards of Reporting Trials guidelines [28,29] (Multimedia Appendix 1). We will conduct a single site, assessor-blinded, parallel group, randomized controlled feasibility trial using a 1:1 allocation into an immediate intervention condition or a delayed intervention condition. A delayed intervention condition was deemed appropriate for PAT-MS based on the decision framework for appropriate control conditions for behavioral intervention trials [30,31].

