### Participants

#### Sample Size

As a feasibility trial, this study will provide robust estimates of the likely rates of recruitment and retention as well as estimates of the variability of the proposed scientific outcomes to inform a well-designed pilot RCT. With these considerations in mind, our goal is to recruit 10 people with MS–care partner dyads per condition within a 6-month recruitment window, consistent with sample size guidelines for feasibility trials [32] and previously published exercise trials for people with advanced MS [33]. Enrolling 10 dyads per condition will account for approximately 15% attrition rate, as recommended for feasibility trials [34].

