The randomization sequence will be generated by an independent biostatistician using 1:1 permutated block randomization. Variable-sized blocks will be used to ensure approximately equal numbers in the 2 trial conditions. Participants will then complete the immediate intervention condition or the delayed intervention condition (ie, maintenance of usual activities) for 12 weeks. The same scientific feasibility outcomes as the baseline will be repeated immediately after the intervention (T2). We anticipate that each assessment session will last for approximately 2 hours. At the completion of the intervention, participants will also be asked to complete a satisfaction survey and an individual exit interview to assess their satisfaction with specific intervention components (ie, intervention content, interventionist, and delivery method) and their subjective experiences of participation in all aspects of PAT-MS, respectively. People with MS and their care partners will complete the same surveys. We anticipate that the survey will take approximately 15 minutes to complete. Individual exit interviews will be conducted over the phone by a member of the research team and will last for approximately 30 minutes. The same interview guide will be used for people with MS and their care partners. Participants in the delayed intervention condition will receive the intervention after the postintervention assessment (T2). We will follow the same intervention delivery procedures for the delayed condition as for the immediate intervention condition.

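### The treatment effect is quantified only as a within-condition Cohen d, so the randomised contrast between immediate and delayed intervention is never estimated

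*Protocol article*

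**What the plan says.** All references are to the protocol article.

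- **Study Design:** a "randomized controlled feasibility trial using a 1:1 allocation into an immediate intervention condition or a delayed intervention condition".
- **Study Procedures:** the delayed arm spends the T1–T2 interval on usual activities and receives the intervention only after T2. It is therefore an untreated concurrent control over the period analysed.
- **Scientific Outcomes:** "These will include assessing safety, treatment effect, participant satisfaction with intervention components", among others. Treatment effect is a declared outcome.
- **Treatment Effect:** "This will involve assessing changes in the following outcomes between T1 (baseline) and T2 (12 weeks"), followed by the list of measures. The definition is a change over time and does not mention the other condition.
- **Quantitative Data Analysis:** the only effect measure is Cohen's *d* for change over time: "Within-subject changes and effect sizes for improvement in scientific outcomes from T1 to T2 will be calculated using Cohen". The article then sets the level at which this statistic is obtained, namely inside each combination of role and arm: "separately for people with MS and care partners and by condition (immediate vs delayed control").
- **Sample Size:** "our goal is to recruit 10 people with MS–care partner dyads per condition within a 6-month recruitment window", with an allowance of about 15% attrition.

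No section states a difference between conditions, a between-group effect size, a baseline-adjusted comparison or an interval for a contrast.

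**The concern.** A randomised control arm serves to remove change that has nothing to do with the intervention. The analysis as worded does not use it that way. Each *d* is a before-and-after comparison inside one arm. It absorbs whatever else moves scores over 12 weeks, such as repeat assessment, the effect of being measured, or regression to the mean in people selected because they were inactive (Recruitment and Enrolment), so far as that selection still affects T1. Calling that quantity a treatment effect invites readers to credit all of it to the intervention.

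This is not a detail left for an analysis plan. The article chooses the quantity, and chooses one that does not match the design. At stake are how the scientific outcomes are interpreted and what is taken from them into the pilot RCT.

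**Working it through.** **No plan figure to reproduce.** The sample size rests on feasibility guidelines; no alpha, power, effect size or SD is given. The two calculations below show what the stated quantity measures and how precisely the missing one could be estimated.

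**Inputs.**
- From the article: *n* = 10 per condition. About 15% attrition leaves 10 × 0.85 = 8.5 per condition.
- From Table 2, as stand-ins for the T1–T2 correlation *r*: test-retest ICCs of 0.84 (accelerometer) and 0.74 (self-reported activity). The article does not say that either is a 12-week correlation. Table 2 also gives a rank correlation of 0.49 for the accelerometer.
- Assumed: *r* = 0.5 as a lower value (close to that 0.49), and a shift *c* of 0.2 to 0.5 baseline SD common to both arms and unrelated to the intervention.

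**1. What each quantity estimates when the true effect is zero.** Each arm's mean change is *c*.
- Within-condition *d* on the baseline SD = *c*, that is 0.20 to 0.50.
- Within-condition *d* on the SD of change = *c* / √(2(1 − *r*)). This runs from 0.2 / √(2 × 0.5) = 0.20 to 0.5 / √(2 × 0.16) = 0.88.
- Immediate minus delayed = *c* − *c* = 0 for every *c* and *r*.

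A simulation (20,000 runs, 10 per arm, *c* = 0.3, zero true effect, baseline SD) agrees. The mean *d* is 0.33 in each arm and the mean between-condition effect is 0.00. The excess of 0.33 over 0.30 is small-sample bias: 0.3 / 0.914 = 0.33, with 1 − 3/(4 × 9 − 1) = 0.914.

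| *r* | Immediate-arm *d* ≥ 0.2 | Between-condition *d* ≥ 0.2 |
|---|---|---|
| 0.5 | 63% | 33% |
| 0.74 | 67% | 27% |
| 0.84 | 72% | 22% |

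The contrast is noisy too, but it is centred on the right value.

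**2. Precision of the contrast, in baseline SD.**
- Adjusted for T1: half-width ≈ *t*(0.975, 2*n* − 3) × √(1 − *r*²) × √(2/*n*). With *n* = 10 and *r* = 0.84: 2.11 × 0.543 × 0.447 = 0.51.
- Difference in change: half-width = *t*(0.975, 2*n* − 2) × √(2(1 − *r*)) × √(2/*n*). With *n* = 10 and *r* = 0.84: 2.10 × 0.566 × 0.447 = 0.53.

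| *r* | Adjusted, *n* = 10 | Change difference, *n* = 10 | Adjusted, *n* = 8 | Change difference, *n* = 8 |
|---|---|---|---|---|
| 0.84 | 0.51 | 0.53 | 0.59 | 0.61 |
| 0.74 | 0.63 | 0.68 | 0.73 | 0.77 |
| 0.5 | 0.82 | 0.94 | 0.94 | 1.07 |

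These figures treat participants of one role as independent. Any similarity among dyads sharing a teleconference group would widen them.

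**The case against.** The strongest reply is that little depends on this quantity. The objective is feasibility, no hypothesis test is planned, and none of the five criteria in Determining Progression to a Definitive Trial uses an efficacy result. Sample Size names recruitment, retention and outcome variability as what informs the pilot RCT, not effect sizes. And *d* is reported for the delayed arm as well, so a shift shared by both arms would be in plain view. All of this stands, and it limits the severity. It does not supply the missing estimate. The words in brackets label the two strata and specify no contrast, and two values of *d* with different arm-specific SDs, read side by side, give neither a standardised difference nor its uncertainty.

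A reader might infer three stronger points, none of which the article supports.

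- **That the next trial will be under-sized.** The article nowhere plans to put *d* into a sample-size formula. The inflation would also depend on an unstated standardiser and correlation: *d* on the SD of change is 1.77 times *d* on the baseline SD at *r* = 0.84, but 1/√(2 × 0.51) = 0.99 times at Table 2's other value of 0.49. An article may leave the choice of standardiser to the full protocol.
- **That comparing the two *d* values by eye is what generates false differences.** With no effect and a common change of 0.5 SD of change, they differ by at least 0.5 in about 34% of simulated trials. The between-condition standardised difference does so in about 28%. Most of that is small-sample noise. Counting trials in which only one arm's interval excludes zero does not help either, because the article plans no such intervals.
- **That baseline adjustment gains much precision over a difference in change.** The standard errors are 0.24 against 0.25 at *r* = 0.84 and 0.30 against 0.32 at *r* = 0.74. The gain is larger only at lower correlations.

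**Conclusion.** The point holds as a should-fix. The article randomises, declares a treatment effect, and then quantifies only change within each condition. Under zero true effect, a shift of 0.2 to 0.5 baseline SD common to both arms would appear as an immediate-arm *d* of about the same size, while the between-condition effect is 0. The shift sizes are assumptions; the article gives no evidence on how much scores drift. The conclusion that the contrast is missing does not depend on them. The progression decision is unaffected. The consequence is for how the scientific outcomes are read and for what is taken into the pilot RCT.

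**What to change.** In Quantitative Data Analysis, define the treatment effect for each outcome, separately for people with MS and for care partners, as the immediate-minus-delayed difference at T2 adjusted for the T1 value, reported with a 95% CI and no significance test. If it is standardised, divide by the pooled baseline SD and say so. Keep the within-condition changes and *d* as descriptive only. Cross-refer to this definition from the Treatment Effect section, so that the two sections describe the same quantity.

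The cost is wording; T1 and T2 are already collected in both arms. The downside is that the estimate will be imprecise, with a half-width of about 0.5 to 0.8 baseline SD at 10 per arm and wider after attrition, and it will probably look less favourable than a within-condition *d*.

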#### Qualitative Data Analysis

All audiorecorded interviews will be transcribed and anonymized before the analysis. The qualitative analysis will be underpinned by a social constructivism paradigm [67], which will allow exploration of the meaning and understanding of the experiences of our participants relative to participation in PAT-MS. The systematic six-phase process of thematic analysis as described by Braun and Clark [68] will be undertaken. The rigor of the qualitative analysis will be maximized through a range of strategies recommended by Smith and McGannon [69].

### Determining Progression to a Definitive Trial

Progression to a pilot RCT will be considered if minimum success criteria are achieved in key feasibility metrics or if we can identify strategies for overcoming any identified challenges in these areas [70]. These criteria were selected based on the guidelines for prospectively defining progression to future evaluative studies [71,72]. The criteria include the following:

A minimum of 50% of the intended 20 dyads are recruited within a 6-month recruitment windowA minimum of 70% participant complianceStudy satisfaction ≥4/5 on the satisfaction surveyLess than 10% of participants report a serious AELess than 20% participant attrition.

